#### Inclusion criteria

Age: 18 to 65 years;Fitzpatrick skin phototype I-VI [64]Keloid with no type of previous treatment;Recurring keloid after surgical excision;Recurring keloid after use of other therapies and at least three months without treatment.

The proposed clinical trial (S1 and S2 Files) will be conducted in accordance with the precepts stipulated in the Declaration of Helsinki (revised in Fortaleza, 2014) and was approved by the Ethics committees in human research of the Mandaqui Hospital Complex (number: 4.281.616 (S3 File) and of the *Universidade Nove de Julho*, certificate number: 4.594.799 (S4 File). The participants will receive verbal and written clarifications regarding the objectives and procedures; those who agree to participate in the study will sign a statement of informed consent. After the conclusion of the study, the research data will be available in the thesis databank of *Universidade Nove de Julho* (http://www.uninove.br). The participants’ privacy will be preserved, and their data will be used solely and exclusively for the performance of scientific studies, according to the Confidentiality Term. The information will be published in scientific articles and congresses related to the subject, anonymously.

It is also important to note that all research development will be monitored by the researching surgeon doctor and any complications will be promptly attended to according to technical standards.

#### Exclusion criteria

Keloid in treatment;Pregnant and lactating women;Keloid with primary synthesis of the skin and no possibility of excision.Contraindications for undergoing surgery (e.g.: coagulopathies, diabetes myellitus, drug allergies);Contraindications for the use of corticosteroids;All types of Collagenosis.

### Strategies to improve adherence of the participants to the protocol

The participants will be included in a phone message group through which they will be reminded of the follow-up appointments by the researchers. They will also be contacted by the secretaries of the hospital, who will maintain the addresses and contact data of each patient updated.

### Randomization of groups

Block randomization will be performed using a sequence generator program (Research Randomizer, version 4.0, computer software available since June of 2013 at http://www.randomizer.org). The participants will be assigned sequential numbers (1–58). Each patient is going to be allotted an opaque envelop which will contain a piece of paper stipulating to which group it belongs. The envelopes will be sealed until the time of the treatment and their contents will be determined randomly. The patients will be randomly allocated to two groups:The participants will be assigned sequential numbers (1–58). Each patient is going to be allotted an opaque envelop which will contain a piece of paper stipulating to which group it belongs. The envelopes will be sealed until the time of the treatment and their contents will be determined randomly. The patients will be randomly allocated to two groups:

Study group (N = 29): intralesional administration of corticoid and active photobiomodulation in the preoperative and postoperative periods of keloid surgery.Sham group (N = 29): intralesional administration of corticoid and sham photobiomodulation in the preoperative and postoperative periods of keloid surgery.

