### Sample size and participants

The sample size was calculated considering a significance level of 0.05 and 80% power to obtain the means of improvement at three months postoperatively using the Vancouver Scar Scale (corticoid group: mean = 1.95; SD = 1.84) based on the paper by HEWEDY *et al*. [63]. Due to the lack of data in the literature regarding the study group, we estimated the same variability found in Group 1 (G1 1.95 vs. G2 0.25, difference of 1.7). Considering a 10% dropout rate, a total of 58 participants will be recruited: N = 29 per group. All participants will be recruited from the Mandaqui Hospital Complex and Nove de Julho University as well as through announcements in digital media.

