### Statistical analysis

The Kolmogorov-Smirnov test will be used to determine the normality of the data. Variables with parametric distribution will be submitted to one-way analysis of variance (ANOVA) followed by Tukey’s test for comparisons between groups. Variables with nonparametric distribution will be submitted to the Kruskal-Wallis test followed by Dunn’s post hoc text for comparisons between groups. The significance level will be set at α = 5%.

Original study forms will be entered and kept on file at the participating site. When a form is selected, the participating site staff will pull that form, copy it, and sent the copy to the data coordinating center. Participants’ files will be stored in numerical order and stored in a secure and accessible place and manner. They will be maintained in storage for a period of 05 years after completion of the study. The primary author will be responsible for the database on its own device and in the storage cloud. He has no conflicts of interest and no funding.

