## Interventions

### Intralesional administration of corticoid

The participants in both groups will receive an intralesional injection of 20 mg/ml triamcinolone hexacetonide (Triancil^®^, Apsen Farmacêutica S.A.)–two injections in the preoperative period with a two-week interval between injections and a monthly injection for three months in the postoperative period. The injections will be intralesional and will not surpass the dermis. The drug will be diluted with the same quantity of 2% lidocaine. The scar will be divided into equal parts of 1 cm^2^ and the drug will be distributed equally, respecting the total dose per session of 20 mg for the face and 40 mg for other topographies.

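### The fixed VSS comparison is unadjusted although pre-intervention VSS, anatomic site and keloid history are known beforehand: a modest, assumption-dependent loss of precision, not bias

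*Protocol article*

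**What the plan says.** - **Analysis** (Statistical analysis): "Variables with parametric distribution will be submitted to one-way analysis of variance (ANOVA", followed by Tukey's test; variables judged nonparametric go to Kruskal-Wallis with Dunn's test. This is one rule for all variables, and no covariate appears in it.
- **Allocation** (Randomization of groups): "The patients will be randomly allocated to two groups", in blocks, from one series numbered 1 to 58. No stratification factor is named.
- **Site** (Intralesional administration of corticoid): injections are given "respecting the total dose per session of 20 mg for the face and 40 mg for other topographies".
- **History** (Inclusion criteria): untreated keloids are eligible, and so are "Recurring keloid after surgical excision" and recurrence after other therapies.
- **Baseline score** (Questionnaires): surgeons score the VSS before the intervention and at one, three, six and twelve months after surgery.
- **Planning values** (Sample size and participants): "a significance level of 0.05 and 80% power to obtain the means of improvement at three months postoperatively", with "corticoid group: mean = 1.95; SD = 1.84" and "G1 1.95 vs. G2 0.25, difference of 1.7", 10% dropout and 29 per group.

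**The concern.** Three items are in hand before the first injection: the VSS score, whether the keloid is on the face, and whether it has recurred. Site carries a different limit on the background steroid, which both arms receive. History separates patients who have already recurred from those who have not, in a trial whose Discussion names recurrence in its main objective. Each could plausibly explain part of the variation in postoperative VSS.

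A one-factor method leaves that variation in the error term. With 58 patients, one of these features may also fall unevenly between arms. The test stays valid, but a reader of the single observed result may then doubt it, and adjusting only after the data are seen would persuade few. This goes beyond a covariate list left to another document: a covariate model would have to replace the method the article names.

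**Working it through.** **Inputs.** From Sample size and participants: SD 1.84 in both arms ("we estimated the same variability found in Group 1"), difference 1.7, alpha 0.05 (taken as two-sided), 29 per arm, 10% dropout. Evaluable per arm: 29 × 0.9 = 26.1, so 26. Assumed, because the document gives neither: prevalence of each factor (10–50%), and the share R² of within-arm VSS variance explained by the covariates together (0.05–0.30).

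**1. The plan's own figure.** The standardised difference is 1.7 / 1.84 = 0.924. A two-sided t-test with 80% power needs 20 per arm, 23 after dropout, 46 in total, not 58. At 90% power it needs 26, and 26 / 0.9 = 28.9, so 29. The stated 58 therefore matches 90% power. That mismatch is a separate matter; here it means that 26 per arm has about 90% power for 1.7 points without adjustment.

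**2. Precision.** SE = 1.84 × √(1 − R²) × √(2/26). The detectable difference and power use the noncentral t distribution, with 50 degrees of freedom unadjusted and 52 − 5 = 47 adjusted for three covariates.

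| R² | SE | SE reduction | Detectable at 80% power | Power for 1.7 |
|---|---|---|---|---|
| unadjusted | 0.510 | – | 1.46 | 90% |
| 0.05 | 0.497 | 2.5% | 1.42 | 92% |
| 0.10 | 0.484 | 5% | 1.38 | 93% |
| 0.20 | 0.456 | 11% | 1.31 | 95% |
| 0.30 | 0.427 | 16% | 1.22 | 97% |

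Losing three degrees of freedom matters little in itself: at R² = 0 the detectable difference is 1.46 with either count.

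**3. Cost of estimating the coefficients.** The table assumes the covariates are balanced. Averaged over chance imbalance, three covariates in 52 patients inflate the variance by about 1 + 3/(52 − 3 − 3) = 1.065, or 1.032 in SE. A simulation with one continuous and two binary covariates gave the same 1.065. Multiplying by √(1 − R²), the SE changes by about +1%, −2%, −8% and −14% at R² = 0.05, 0.10, 0.20 and 0.30. Break-even is at R² = 1 − 1/1.065 = 0.06.

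**4. How large might R² be?** A binary factor with prevalence p that shifts VSS by g points explains p(1 − p)g²/1.84². For g = 1.0 this is 0.05 at p = 20% and 0.07 at p = 50%. One such factor alone would roughly break even; a clear gain needs stronger or several predictors.

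**5. Chance imbalance.** For 58 patients split 29/29 without strata (hypergeometric; block size is not stated), the probability that a factor differs by 20 percentage points or more is 2%, 10%, 8% and 11% at prevalence 10%, 20%, 30% and 50%. For at least one of two independent factors with prevalence 20–50%, simulation gives 18–21%. A 20-point imbalance in a factor worth 0.5, 1.0 or 1.84 VSS points moves the estimate by 0.20 × g = 0.10, 0.20 or 0.37, which is 6%, 12% or 22% of 1.7. All are below the standard error of 0.51.

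**The case against.** - **Nothing shows that these factors predict VSS.** This stands. A lower steroid limit for the face does not establish a better or worse outcome, and the inclusion list only says who is eligible. The factors can be called plausibly prognostic and no more.
- **A reader might infer that an uneven split would confound the PBM effect with steroid dose.** The document does not support that as a fault in validity. Under randomisation the unadjusted comparison is unbiased, and its type I error already allows for chance imbalance.
- **A reader might infer that allocation should have been stratified by site or history.** The article is silent on strata, but it condenses a fuller protocol that is not shown, and stratifying is a debatable design choice: separate block series with incomplete blocks would no longer guarantee 29 per arm. No finding is made on allocation.
- **Planned power is already exceeded.** True at 1.7 points. But the article concedes a lack of data for the study group, and 1.7 means a fall from 1.95 to 0.25. If the true difference were 1.4, unadjusted power would be 77%, against 81%, 85% and 89% at R² = 0.10, 0.20 and 0.30 (step 2 method, before the cost in step 3).
- **Pre-intervention VSS scores a keloid that is then excised.** This stands: its correlation with the new scar's score may be low. The sample size text speaks of improvement, so a change score may be intended. That would not replace adjustment, because with equal variances a change score adds variance whenever the correlation is below 0.5.
- **The analysis rule is generic, not a dedicated VSS model.** True, but it is the only method named for the VSS, and it has no place for a covariate.

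**Conclusion.** The concern holds for the analysis only, at low severity. The article fixes a valid but unadjusted comparison where an adjusted one could be specified from data already collected. The loss lies in precision and in the credibility of the observed result; it is not bias and not an error in the test. Its size rests wholly on an assumed R². Over 0.05 to 0.30 the standard error would fall by 2.5–16% before the cost of estimating three coefficients, and by between nothing and about 14% after it. The other assumptions are 26 evaluable per arm, a common SD of 1.84 and a two-sided 5% level. The trial's ability to detect 1.7 points is not in danger.

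**What to change.** In Statistical analysis, replace the one-way ANOVA for the VSS with a linear model containing arm, pre-intervention VSS, site (face/other) and keloid history (untreated/recurrent). Fix it before unblinding, and report the adjusted arm difference with its confidence interval. Name a rank-based or robust version of the same model as the sensitivity analysis if residuals are clearly non-normal, so that the present nonparametric branch has a counterpart.

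The inclusion criteria distinguish three histories. Merging the two kinds of recurrence saves a degree of freedom and should be stated as a choice.

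Cost: a change of analysis wording, three degrees of freedom and, on average, about 3% in standard error if the covariates explain nothing. No new data, visits or patients are needed, and the allocation procedure stays as it is.

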### Blinding

The evaluator, analyst, and participants will be unaware of the group to which the participants are allocated. The operator will also be unaware of whether the blue light has a biological or is a placebo effect.

## Evaluations

### Questionnaires

A questionnaire will be administered to the participants to collect their personal information. The determination of skin phototype will performed using the Fitzpatrick classification [64] prior to the onset of the interventions in the participant’s first outpatient appointment by trained health professionals and students.

The *Quality of Life of Patients with Keloid and Hypertrophic Scarring* [5] questionnaire, which has been translated and validated for Portuguese, as well as the *QualiFibro/Plastic Surgery—UNIFESP* questionnaire [65] will be used for the assessment of quality of life. The participants will answer the questionnaires prior to the intervention as well as one, three, six, and twelve months postoperatively. The participants will also answer Part II (classification of satisfaction) of the *Patient Scar Assessment Questionnaire* (PSAQ) [66], which has been translated and validated for Portuguese [67], for the assessment of the quality of the remaining scar one, three, six, and twelve months postoperatively. These questionnaires will be applied in the same way in the periods already explained by trained health professionals and students.

Blinded, calibrated, certified plastic surgeons will answer the *Vancouver Scar Scale* (VSS) [68], which was translated into Portuguese by Santos et al. [69], after the clinical evaluation prior to the intervention as well as one, three, six, and twelve months postoperatively.

### Measurement of keloid and remaining scar

Molds will be made of the scars in light condensation silicone (Zhermack, Badia Polesine, Italy). The material will be stored in acrylic dishes and sent for analysis (optical coherence tomography) for the determination of area and volume. These procedures will be performed in preoperatively as well as one, three, six, and twelve months postoperatively.

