## Abstract

Keloid scars are characterized by the excessive proliferation of fibroblasts and an imbalance between the production and degradation of collagen, leading to its buildup in the dermis. There is no “gold standard” treatment for this condition, and the recurrence is frequent after surgical procedures removal. *In vitro* studies have demonstrated that photobiomodulation (PBM) using the blue wavelength reduces the proliferation speed and the number of fibroblasts as well as the expression of TGF-β. There are no protocols studied and established for the treatment of keloids with blue LED. Therefore, the purpose of this study is to determine the effects of the combination of PBM with blue light and the intralesional administration of the corticoid triamcinolone hexacetonide on the quality of the remaining scar by Vancouver Scar Scale in the postoperative period of keloid surgery. A randomized, controlled, double-blind, clinical trial will be conducted involving two groups: 1) Sham (n = 29): intralesional administration of corticoid (IAC) and sham PBM in the preoperative and postoperative periods of keloid removal surgery; and 2) active PBM combined with IAC (n = 29) in the preoperative and postoperative periods of keloid removal surgery. Transcutaneous PBM will be performed on the keloid region in the preoperative period and on the remaining scar in the postoperative period using blue LED (470 nm, 400 mW, 4J per point on 10 linear points). The patients will answer two questionnaires: one for the assessment of quality of life (Qualifibro-UNIFESP) and one for the assessment of satisfaction with the scar (PSAQ). The team of five plastic surgeons will answer the Vancouver Scar Scale (VSS). All questionnaires will be administered one, three, six, and twelve months postoperatively. The keloids will be molded in silicone prior to the onset of treatment and prior to excision to assess pre-treatment and post-treatment size. The same will be performed for the remaining scar at one, three, six, and twelve months postoperatively. The removed keloid will be submitted to histopathological analysis for the determination of the quantity of fibroblasts, the organization and distribution of collagen (picrosirius staining), and the genic expression of TGF-β (qPCR). All data will be submitted to statistical analysis.

**Trial registration:** This study is registered in ClinicalTrials.gov (ID: NCT04824612).

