Studies have reported the benefits of PBM on the healing process of postoperative scars from different types of surgery, demonstrating the safety and effectiveness of this form of therapy [42–51]. *In vitro* experimental studies using fibroblasts from keloids and human dermis have also demonstrated positive effects, such as an increase in the apoptosis rate and reduction in the cell division rate of these fibroblasts as well as reductions in the synthesis of collagen and the expression of TFG-β [10, 52–59].

Blue light (wavelength ranging from 410 to 480 nm), in particular, is reported to have in inhibitory effect on fibroblasts and TGF-β when administered with a higher energy density (up to 640 J/cm^2^) [10, 52–59].

It is possible that blue light interacts with mitochondrial chromophores in the same way as red and infrared light, as heme centers in cytochromes have significant peak absorption that coincides with the Soret band of porphyrins [60]. In the blue light spectrum, porphyrins and flavoproteins, such as NADH-dehydrogenase and succinate dehydrogenase, can function as photoreceptors [61].

An important aspect to emphasize is the low cost of the LED, as many studies show that in photobiomodulation it has the same effect as lasers [62].

Studies reporting the beneficial effects of PBM on the healing process suggest a promising path for the establishment of this therapeutic modality in the treatment of keloids. Therefore, the purpose of this study is to determine through a randomized and controlled clinical trial the effects of the combination of PBM with blue light and the intralesional administration of the corticoid triamcinolone hexacetonide on the quality of the remaining scar by Vancouver Scar Scale in the postoperative period of keloid surgery. Also, the recurrence rate, its volume, the histopathological analysis, and thequality of life.

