### Photobiomodulation protocol

PBM will be administered in four sessions with a two-week interval between sessions preoperatively as well as immediately after surgery, weekly in the first month postoperatively, at two-week intervals in the second month, and a single session in the third month. The light source will be blue LED (Quantum, Ecco^®^) using the parameters listed in Table 1. In the sham group, the light will be the same color but without power and, consequently, without any biological effect.

**Table 1 pone.0263453.t001:** Dosimetric parameters of photobiomodulation protocol.

Dosimetric parameters	Type of source: LED
Central wavelength [nm]	470
Operating mode	Continuous
Mean radiant power [W]	0.4
Aperture diameter [cm]	1.7
Power density at aperture [W/cm^2^]	0.17
Beam spot on target [cm^2^]	2.268
Irradiance on target [W/cm^2^]	0.176
Useful exposure time [s]	Varying according to size of scar, 60 s per linear cm. Ex.: 1 c m = 60 seg; 10 cm = 600 s.
Exposure time [s]	60 per linear cm
Energy density at aperture [J/cm^2^]	10.58
Radiant energy [J]	Varying with size of scar, according to duration of useful exposure (Item 9). Ex.: 1 cm = 4 J; 10 cm = 240 J
Energy per point [J]	4J
Application technique	Contact
Anatomic location of application points	On remaining scar
Number and frequency of treatment sessions	Preoperative: every two weeks for 30 days. Postoperative: Immediately after surgery, weekly for 4 weeks, every two weeks for another 4 weeks, and one session in 3^rd^ month.

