### Surgical procedure

The surgical excision of the keloid will be performed in a standard manner with resections in a spindle shape or ellipse with a 5-mm margin of healthy skin measured after the end of the scar. Regarding depth, the entire scar tissue should be excised until reaching healthy, fibrosis-free tissue. Hemostasis will be performed carefully with low energy to avoid excessive tissue damage.

The suturing of the surgical wound will be performed using thread with little tissue reaction. For subcutaneous tissue, polyglecaprone absorbable thread 25 (Caprofyl^®^, 4–0 diameter) and a circular needle will be used. If necessary, subdermal stitches will be performed with nylon thread (diameter 4–0 to 6–0). Smaller diameters (5–0 and 6–0) will be used at anatomic sites with less tension and thinner skin and the larger diameter (4–0) will be used at sites with greater tension and thicker skin. For the skin, intradermal sutures will be performed using nylon thread with a diameter of 4–0 at anatomic sites with greater tension and thicker skin and 5–0 at anatomic sites without tension and thinner skin. The scar will be cleansed with 0.9% saline solution and dried followed by the placement of micropore strips in an “x” over the entire scar [70]. These procedures will be standardized and performed in the same way in both groups.

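### Postoperative mold area and volume carry the size of the excised keloid, and the stated unadjusted test leaves that variation in the error term: a loss of precision, not a bias

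*Protocol article*

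**What the plan says.** All citations are to the protocol article.

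- **Measurement of keloid and remaining scar:** molds are "sent for analysis (optical coherence tomography) for the determination of area and volume". On timing: "These procedures will be performed in preoperatively as well as one, three, six, and twelve months postoperatively". No other summary of the mold is named.
- **Abstract:** there are two preoperative molds: "The keloids will be molded in silicone prior to the onset of treatment and prior to excision to assess pre-treatment and post-treatment size". The later molds are of a different object: "The same will be performed for the remaining scar at one, three, six, and twelve months postoperatively".
- **Surgical procedure:** between the two phases all scar tissue is removed, by "resections in a spindle shape or ellipse with a 5-mm margin of healthy skin measured after the end of the scar".
- **Photobiomodulation protocol, Table 1:** exposure time is "Varying according to size of scar, 60 s per linear cm", with worked examples of 1 cm and 10 cm. Staff therefore need a scar length to deliver treatment.
- **Inclusion and exclusion criteria:** no limit on keloid size is given, apart from excluding keloids that cannot be excised.
- **Introduction:** volume and recurrence are aims beside the Vancouver Scar Scale: "Also, the recurrence rate, its volume, the histopathological analysis".
- **Statistical analysis:** "Variables with parametric distribution will be submitted to one-way analysis of variance (ANOVA) followed by Tukey’s test for comparisons between groups", with Kruskal-Wallis and Dunn's test as the nonparametric alternative. Neither takes a covariate.

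**The concern.** The preoperative molds show a keloid; the postoperative molds show the surgical scar that replaced it. The length of that scar depends on the lesion removed plus the margin. Two patients whose scars have the same width and height will differ in area and volume if one keloid was longer than the other.

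The stated test treats all of this between-patient variation as error, although a pre-treatment measurement that could explain part of it is already being taken. Histology and TGF-β come from the removed keloid, and the Vancouver scale and the patient questionnaires are ratings. The molds are thus the only instrument-based measure of the postoperative scar. At stake is whether a real difference in the scar can be seen on that measure with 29 patients per group, and whether an arm that happened to draw shorter keloids could look better on it.

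**Working it through.** **Is there a figure to reproduce?** No. The only sample-size calculation is for the Vancouver scale at three months. Area and volume have no sizing and no stated spread, so everything below rests on assumptions.

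**Inputs from the document.** 29 per group and 10% dropout: 29 × 0.9 = 26.1, so about 26 completers per group. Alpha is 0.05, taken as two-sided. Scar length in the worked example runs from 1 to 10 cm.

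**Assumptions.** Area = length × width and volume = length × width × height, with the three dimensions independent and log-normal. Width CV is 0.3, height CV 0.3 to 0.8, length CV 0.3 to 1.0. For orientation, lengths spread evenly over 1 to 10 cm have mean 5.5 and SD 9/√12 = 2.60, a CV of 0.47, so 0.5 is used as the central case.

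**Step 1: share of variance due to length.** On the log scale each dimension contributes ln(1 + CV²): 0.086 at CV 0.3, 0.223 at 0.5, 0.495 at 0.8, 0.693 at 1.0. With length CV 0.5:

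- area: 0.223 / (0.223 + 0.086) = 72%
- volume, height CV 0.3: 0.223 / 0.395 = 56%
- volume, height CV 0.5: 0.223 / 0.532 = 42%
- volume, height CV 0.8: 0.223 / 0.804 = 28%

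Over the full assumed range the share is 50 to 89% for area and 13 to 80% for volume. Raw volume therefore has 1/(1 − 0.13) = 1.15 to 1/(1 − 0.80) = 5 times the variance of volume per cm. Setting the spread of volume per cm directly at CV 30 to 40%, with length CV 30 to 70%, gives 1.58 to 5.6 by 1 + ln(1 + CV_length²)/ln(1 + CV_percm²).

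**Step 2: what this does to power.** Take a true 30% lower height, a log difference of −ln 0.7 = 0.357, length CV 0.5 and 26 completers per group. Power = Φ(0.357/√(2v/26) − 1.96), where v is the log variance of the outcome.

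| Height CV | v, raw volume | Power, raw volume | v, length removed | Power, length removed |
|---|---|---|---|---|
| 0.3 | 0.395 | 0.53 | 0.172 | 0.87 |
| 0.5 | 0.532 | 0.42 | 0.309 | 0.64 |
| 0.8 | 0.804 | 0.30 | 0.581 | 0.39 |

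The last column is a ceiling for covariate adjustment, because pre-treatment mold size is only a proxy for scar length. If it captured half of the length variance, v would fall by 0.223/2 = 0.112 and power would be 0.67, 0.51 and 0.34.

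**Step 3: chance imbalance.** The difference between arms in mean log length has SD √(2 × 0.223/29) = 0.124 at length CV 0.5. A 1.96-SD imbalance multiplies the ratio of geometric mean lengths by exp(1.96 × 0.124) = 1.28. The same calculation gives 1.16 at CV 0.3 and 1.54 at CV 1.0. For comparison, the assumed treatment effect is a ratio of 0.70.

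**Step 4: which reference mold precedes treatment.** By the text of the photobiomodulation section the sessions are 4 preoperative, 1 immediately after surgery, about 4 in month 1, about 2 in month 2 and 1 in month 3, about 12 in all. About 4 + 1 + 4 = 9 of them precede or coincide with the month-1 mold. Only the mold made before treatment starts is free of treatment.

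**The case against.** The strongest reply is that much of this is unstated rather than wrong. The article is a condensed account, and covariates, scaling and the choice of baseline may be set in a fuller document. That stands in part: the missing details are not themselves the point. But the article does name the measurement and the test, and that test leaves lesion size in the error.

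Four stronger readings are tempting, and the documents do not support them.

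- **Area and volume say nothing about whether the scar is raised or regrowing.** Too strong. Volume includes height: a flat scar has little raised volume at any length, and regrowth adds volume. Four molds of the same scar can also show regrowth within a patient. The dependence on length is greater for area.
- **The plan reads the drop from keloid to scar as benefit.** No contrast across surgery is stated. The abstract keeps the keloid molds and the scar molds apart.
- **The comparison is biased.** Allocation is randomized and surgery is standardized across arms, so original lesion size is balanced in expectation. An unadjusted test keeps its error rate; what suffers is precision and the credibility of a single estimate under chance imbalance.
- **A shorter incision after preoperative light is a confounder.** It would be an effect of the randomized strategy, which starts before surgery. It needs correct labelling, not removal.

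The last item also limits the remedy. Scar length is fixed after the preoperative sessions, so dividing by it removes any effect acting through a smaller excision. Volume divided by area can miss lateral regrowth. For these reasons neither should replace raw volume as the main comparison.

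**Conclusion.** The point holds as one of efficiency and interpretation. Postoperative area and volume depend in part on the size of the excised keloid, and the stated between-group test does nothing about it. In the central illustration (length CV 0.5) length accounts for about 72% of log-area variance and 28 to 56% of log-volume variance, and removing it would raise power for a 30% height difference from 0.30–0.53 to 0.39–0.87. With a small length spread and a wide height spread the share for volume falls to 13%, and the gain would be modest.

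These sizes rest on assumed, independent log-normal dimensions; the direction does not. The change is worth making because it uses data already planned. It does not affect the Vancouver scale comparison on which the trial is sized.

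**What to change.** 1. Compare the arms on postoperative area and on volume at 1, 3, 6 and 12 months, on the log scale if skewed, with the pre-treatment mold area or volume as covariate. The evaluation section should say, as the abstract does, that one preoperative mold is made before any treatment, and name it as the covariate.
2. Report volume per cm of scar length beside raw volume as a supporting outcome for scar quality. State that length is fixed after the preoperative light sessions, so this outcome excludes any effect acting through a smaller excision.
3. Use the pre-treatment and pre-excision molds only for the preoperative-phase comparison between arms, and state that change across surgery is not interpreted as treatment benefit.
4. Treat change from month 1 to months 3, 6 and 12 as descriptive of regrowth, because most light sessions precede the month-1 mold.

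Cost: slightly more analysis work, and recording a length that staff already need to set exposure time. No new procedure or visit is required.
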